## Abstract

**Introduction:**

Delayed diagnosis of diabetic retinopathy (DR) remains a significant challenge, often leading to preventable blindness and visual impairment. Given that physicians are frequently the first point of contact for people with diabetes, there is a critical need for integrated screening programs within diabetes clinics to enhance DR management and reduce the risk of severe vision loss.

**Methods and analysis:**

We will conduct a prospective cohort study comparing (i) the intervention cohort, screened at diabetes clinics and referred to eye clinics per the proposed pathway, and (ii) the standard-of-care (SOC) eye clinic cohort. The study will be conducted in Hyderabad, India, at LV Prasad Eye Institute and four IDEA (Institute of Diabetes, Endocrinology, and Adiposity) Clinics. The primary objective is to evaluate the effectiveness of a systematic diabetic retinopathy screening program in achieving earlier detection and reducing visual impairment among People With Diabetes (PWD) attending IDEA clinics compared to routine care at eye care settings. The screening program will be operationalized using AI-enabled tools and supported by trained non-medical technicians. We will perform visual acuity tests and non-mydriatic fundus photography using AI-assisted cameras. DR-positive patients will be referred for treatment and follow-up. We aim to achieve high accuracy (>90%) in appropriate referral of DR and high screening coverage (>80%) of eligible PWD. Success metrics include screening uptake, AI diagnostic accuracy, referral rates, cost-effectiveness, patient satisfaction, follow-up adherence, and long-term outcomes.

**Conclusion:**

This study aims to enhance diabetic retinopathy screening and management through an AI-enabled approach at diabetes clinics, improving early detection and care pathways. The findings will contribute to evidence-based strategies for optimizing DR screening and management, with results disseminated through peer-reviewed publications to inform policy and practice.

**Trial registration:**

**Trial registration number:** CTRI/2024/03/064518 [Registered on: 20/03/2024] (https://ctri.nic.in/).

## Introduction

Diabetes Mellitus (DM) is a major public health problem worldwide, affecting over half a billion people (537 million in 2021), with projections indicating an increase to 783 million by 2045. Half of these individuals reside in the USA, China, and India [1]. In 2023, it is estimated that India is home to 101.3 million people with diabetes mellitus (DM) and 136.0 million people with pre-diabetes [2]. Diabetic retinopathy (DR) is a significant microvascular complication of DM, caused by damage to the blood vessels in the retina, leading to vision loss or blindness. The prevalence of DR is increasing due to the rising incidence of diabetes, making it a leading cause of blindness globally and in India [3].

A nationwide multicentric study in India found the prevalence of DM in adults aged 40 years and older to be 18%, DR at 12.3%, and vision-threatening diabetic retinopathy (VTDR) at 4%, estimating 3 million people with VTDR in India [4]. The estimated national prevalence of vision impairment among people with known or undiagnosed diabetes was 21.1% (95% CI (confidence intervals) 15.7–27.7) and blindness was 2.4% (1.7–3.4). A higher prevalence of any vision impairment (30%) and blindness (6.7%) was observed in those with ungradable images (indicating cataract burden). Among known diabetics, vision-threatening diabetic retinopathy and diabetic macular oedema were associated with blindness. Based on the estimated 101 million people with diabetes in 2021, approximately 21 million people in India have vision impairment due to diabetes, of whom 2.4 million are blind, with a higher prevalence observed in those from lower socioeconomic strata [5]. Landmark trials over decades have shown that early detection and treatment of DR can prevent or delay its progression and reduce the risk of vision loss [6–8]. For people with diabetes aged 40 years or above, annual screening followed by eye examinations would cost around 42.3 billion Indian rupees (INR) per year; treating sight problems around 2.87 billion INR per year if 20% of those needing treatment receive it; and lost economic activity around 472 billion INR. Moreover, 2.86 million quality-adjusted life years (QALYs) are lost annually due to blindness and moderate-severe visual impairment (MSVI) [9].

The effectiveness of systematic DR screening programs in reducing blindness due to DR has been established in high-income countries [10]. Targeted telemedicine-based screening and referral of people with diabetes have been shown to be more effective than universal referral for DR screening in India [11,12]. However, there is a lack of large-scale systematic screening initiatives in low- and middle-income countries like India [13]. India’s complex and fragmented healthcare delivery system presents a spectrum of contrasting landscapes, including socioeconomic factors, issues with medical infrastructure, insufficiencies in the supply of medical requisites, and economic disparities in diabetes care delivery between government and private sectors [14,15]. The absence of systematic screening programs in India results in many undiagnosed cases of DM and DR, leading to delays in treatment. The lack of access to timely treatment can cause irreversible vision loss and increase the burden on the healthcare system. The situation is compounded by the lack of awareness of DR among people with diabetes and the limited availability of ophthalmologists in many parts of the country [16,17]. With a ratio of 18 ophthalmologists per million population, each ophthalmologist in India is required to examine 3500 people with diabetes annually [18,19]. The actual number would be higher due to several nonpracticing ophthalmologists and people at risk of developing diabetes. Additionally, there are only 1100 registered retinal specialists [20].

To address this problem, effective screening programs are needed to detect DR early and provide timely treatment. Implementing such programs requires a collaborative effort from healthcare providers, policymakers, and the community. Innovative technologies, such as telemedicine and artificial intelligence, could significantly improve the detection and management of DR in low-resource settings [21,22]. Providing one-stop care at a diabetes clinic for complications of diabetes, including DR, can also help address the problem by offering comprehensive care that includes screening, diagnosis, and treatment for DR and other complications of diabetes, ensuring timely and coordinated care that can improve outcomes and reduce the burden on the healthcare system.

Physicians play a pivotal role in screening for diabetic retinopathy (DR), as they are often the initial point of contact for individuals with diabetes. Integrating DR screening within a physician’s office has proven to be more effective than traditional self-reported screening models [11,23]. To effectively manage Diabetic complications like DR, implementing a systematic DR screening program at the physician clinic level is an optimal strategy. Fundus photography-based models are particularly effective for DR screening, as they allow for objective assessment [12,24]. Utilizing non-mydriatic fundus cameras with built-in artificial intelligence algorithms in physician offices enables trained technicians to capture images efficiently.

In India, established guidelines for DR screening are in place, and a recent positive development is the inclusion of DR screening in the Ayushman Bharat Pradhan Mantri Jan Arogya Yojana (AB PMJAY) [25,26]. Under this program, both ophthalmologists and general physicians are eligible for reimbursement for DR screening services. The literature offers insights into DR screening guidelines [27,28], the feasibility of telemedicine referral pathways between diabetes and ophthalmology clinics [12], and the inclusion of DR screening reimbursement under AB PMJAY [29]. However, there remain gaps in evidence, particularly regarding disease staging, operational and clinical outcomes of subsequent treatment and follow-up, and the cost-effectiveness of the referral pathway for both healthcare providers. The objective of the present study is to address these gaps and optimize strategies for DR screening and management.

### Study hypothesis

This study aims to investigate whether implementing a systematic DR screening program at the physician clinic can lead to earlier detection of blindness and visual impairment caused by DR compared to routine DR care pathways at a tertiary eye care setting. As the physician is typically the first point of contact for people with diabetes, implementing such a program may improve the overall management of DR and reduce the risk of severe vision loss. This study could help in the development of more effective DR screening and management strategies, improving outcomes for people with diabetes.

### Objectives

The study aims to show that systematic screening leads to earlier detection of diabetic retinopathy (DR) and reduces visual impairment. It will compare the effectiveness of screening at physician clinics versus routine DR care in eye care settings. The screening program, supported by trained non-medical technicians, is AI-enabled and targets over 90% accuracy in appropriate referral of DR and 80% coverage of eligible people with diabetes (PWD).

The secondary objectives of the study are to: 1. Assess the cost-effectiveness of the AI-enabled systematic screening program and referral pathway compared to the current pathway at an eye care clinic. 2. Evaluate patient satisfaction and adherence to follow-up recommendations in the AI-enabled screening program versus the routine care pathway through an effective digital tracking system.

## Methods and analysis

### Study design

We will conduct a prospective cohort study involving a comparison between two patient groups: (i) intervention cohort: patients screened at the diabetes clinics using AI and trained nonmedical technicians and referred to the eye clinic as per the proposed pathway, and (ii) standard-of-care (SOC) cohort: patients who arrive at the ophthalmology clinic as per current practice - either self-walk-ins or referrals from other healthcare providers. Fig 1 shows SPIRIT template for clinical trial.

**Fig 1 pone.0324382.g001:**
[figure not shown]
SPIRIT template for clinical trial.

### Study setting

All the study sites will be in the city of Hyderabad in Telangana, India (study area map: Fig 2)

**Fig 2 pone.0324382.g002:**
[figure not shown]
Study area map.

•LV Prasad Eye Institute (Kallam Anji Reddy Campus at Banjara Hills) (Tertiary eye clinics)•IDEA Clinics (Madhapur, Kondapur, Ameerpet, Kukatpally Housing board (KPHB) (Diabetes clinics)

The LV Prasad Eye Institute is a leading tertiary eye care center with advanced infrastructure for diabetic retinopathy diagnosis and treatment, making it an ideal reference for validating the intervention. The IDEA Clinics are strategically located in urban areas with a high burden of diabetes and diabetic retinopathy, ensuring the recruitment of a relevant and representative population. These clinics provide comprehensive diabetes care and offer an optimal setting to test the integration of AI-enabled diabetic retinopathy screening within existing care pathways. The combination of these sites allows for the evaluation of the intervention’s feasibility and scalability in diverse healthcare settings, supporting its potential for broader implementation.

The Indian School of Business team will oversee project management, research methodology, data analysis, and cost-effectiveness analysis, leveraging their management and research expertise to enhance the collaboration.

### Selection of participants

The inclusion criteria for this study in the intervention arm are People with Diabetes (PWD) who visit the diabetes clinics who have never had a fundus examination or fundus photo screening IDEA clinics (Diabetes clinics)/LVPEI(Eye clinics). The referral source will be captured as self-reported, physician, LVPEI network, or ophthalmologist in the standard of care arm -LVPEI eye clinic pathway.

The exclusion criteria for the study are designed to omit individuals with previously diagnosed Diabetic Retinopathy (DR) at the time of presentation to diabetes clinics during the study period. Although we will not include the images of these patients in the study analysis, we will offer appropriate care for their DR at the eye clinic. Additionally, we will seek consent from all eligible participants before they are enrolled in the study and subjected to study protocol. Participants enrolled in the project will be between 18 and 90 years of age.

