### Sampling

The study will employ a **convenience sampling method**, recruiting all consecutive eligible individuals with diabetes mellitus (DM) visiting physician clinics and eye care settings who meet the standard inclusion and exclusion criteria and provide informed consent. While convenience sampling is utilized, potential sources of bias include **selection bias, site-specific variation, differential access to care and Observer Bias**. To mitigate these, systematic recruitment will be ensured by enrolling all eligible patients consecutively at each site, reducing the likelihood of preferential selection. Recruitment will take place across multiple physician clinics and eye care settings to improve representativeness and minimize site-specific variation. Differential access to care will be monitored by assessing demographic and clinical characteristics of enrolled participants, allowing adjustments to recruitment strategies if needed. To prevent observer bias, standardized screening protocols and training for healthcare personnel will be implemented, ensuring consistency in recruitment and data collection. These measures aim to enhance the validity and generalizability of the findings while acknowledging the inherent limitations of convenience sampling.

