### Sample size

We calculate the sample size to detect meaningful differences in the disease staging of patients between two arms at their first eye consultation. Based on the historic data from LVPEI, we assume a 50% prevalence of STDR among DR patients in the SOC arm. Also, we assume that the prevalence of STDR in the intervention arm at the time of screening in the diabetes clinic would be much lower (approximately 10%). However, patients in early stages of DR may not comply with the referral and hence the prevalence of STDR among patients who complete their first ophthalmology visit may be higher (approximately 25%). Based on these estimates, to achieve a power of 80% with a Type-I error rate of 5%, we estimate a sample size of 60 patients in each arm. Since the additional intervention required for the study is minimal (a short check-up using a camera), we expect that about 80% of the eligible patients will consent to participate. Thus, we will need 75 patients with DR to be identified in the intervention arm. Further, based on the historic data at the IDEA clinics, we estimate that 20% of all new registering diabetic patients will have DR. Thus, we will plan to register and screen 375 new diabetic patients each at IDEA clinics (intervention) and LVPEI clinics (SOC arm).

To evaluate the AI tool’s diagnostic accuracy with sensitivity and specificity set at 80%, a sample size of 246 DR-positive cases is required for sensitivity analysis, and 246 DR-negative cases for specificity analysis, assuming a 95% confidence level and a margin of error of ±5%.Given the estimated 20% prevalence of diabetic retinopathy (DR) in the screened population, a total of 1230 patients will be screened to ensure adequate representation of both DR-positive and DR-negative cases.

To assess patient satisfaction, a sample size of **316 patients** will be selected from both the AI-enabled and routine eye care pathways, calculated to detect a difference in satisfaction rates (80% vs. 65%) with a **95% confidence level** and a **margin of error of ±5%**. Random sampling will be employed to ensure unbiased selection of participants from each pathway. This method will involve assigning unique identifiers to eligible patients and using a randomization tool to select participants, ensuring the sample is representative of the study population.

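### The never-examined and no-prior-DR conditions are written only for the diabetes clinics, so the SOC arm can include already-examined referrals and the 50% versus 25% STDR contrast mixes pathway effect with eligibility

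*Protocol article*

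**What the plan says.** In the protocol article, Selection of participants opens: "The inclusion criteria for this study in the intervention arm are People with Diabetes (PWD) who visit the diabetes clinics". The same sentence limits entry to those with no earlier fundus examination or photograph. The exclusion criteria are there to "omit individuals with previously diagnosed Diabetic Retinopathy (DR) at the time of presentation to diabetes clinics during the study period". For the SOC arm the section says only which referral sources will be recorded: "The referral source will be captured as self-reported, physician, LVPEI network, or ophthalmologist in the standard of care arm". The age range of 18 to 90 is the one criterion given for all participants.

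Study design describes the SOC cohort as "patients who arrive at the ophthalmology clinic as per current practice - either self-walk-ins or referrals from other healthcare providers".

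Sampling says that consecutive patients will be recruited, "visiting physician clinics and eye care settings who meet the standard inclusion and exclusion criteria and provide informed consent", but lists no criteria of its own.

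Sample size sets the numbers to "detect meaningful differences in the disease staging of patients between two arms at their first eye consultation". It assumes 50% STDR among DR patients in the SOC arm, from historic LVPEI data. In the intervention arm it assumes about 10% at screening, and about 25% among those who complete the first ophthalmology visit.

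**The concern.** Followed as written, the two arms have different entry rules. A diabetes-clinic patient with any earlier fundus examination, or with known DR, is out. A patient with the same history who reaches LVPEI on an ophthalmologist's referral is in. Such a patient has probably had an eye consultation already, and may have been sent on because disease was found. Stage at LVPEI is then not stage at first detection.

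Earlier detection is the primary objective, and the staging contrast is its main test. If the SOC arm carries known, more advanced cases that the intervention arm excludes by rule, a lower STDR share in the intervention arm cannot be credited to screening alone. The Cost-effectiveness analysis section plans to model the benefit of earlier diagnosis, so the same distortion could carry into the cost per QALY. A larger sample would not remove it.

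**Working it through.** **1. The plan's own figure.** Inputs from Sample size: 50% versus 25%, 80% power, 5% type I error (taken as two-sided; the article does not say), equal arms. With the pooled normal formula and no continuity correction:

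n = [1.960 × √(2 × 0.375 × 0.625) + 0.842 × √(0.50 × 0.50 + 0.25 × 0.75)]² / 0.25² = (1.342 + 0.557)² / 0.0625 ≈ 57.7, so 58 per arm.

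The stated 60 is consistent with this, and power at 60 is 81.6%. The onward steps also hold: 60 / 0.80 = 75 and 75 / 0.20 = 375. The arithmetic is sound. The question is who contributes to the 50%.

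**2. Which condition is stated for which arm.**

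| Condition | Intervention arm | SOC arm |
|---|---|---|
| No earlier fundus examination or photograph | Stated | Not stated |
| No previously diagnosed DR | Stated, at presentation to diabetes clinics | Not stated |
| Age 18 to 90 | Stated | Stated |
| Ophthalmologist or LVPEI-network referral | Not a listed source | Listed source |

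**3. What a mixed SOC arm does to the contrast.** Assume no screening effect, so that comparable DR patients have 25% STDR in both arms. Let f be the share of SOC DR patients who are already-examined referrals, and q their STDR rate. The document gives neither; both are assumptions.

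SOC rate = 0.25 × (1 − f) + q × f

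For f = 30% and q = 75%: 0.25 × 0.70 + 0.75 × 0.30 = 0.175 + 0.225 = 40%.

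The chance of a significant result showing the SOC arm worse, with 60 per arm:

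Φ{[0.15 × √60 − 1.960 × √(2 × 0.325 × 0.675)] / √(0.40 × 0.60 + 0.25 × 0.75)} = Φ{(1.162 − 1.298) / 0.654} = Φ(−0.21) ≈ 42%.

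The range over assumed inputs, by the same formulas:

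| f | q | SOC rate | Chance of significance with no screening effect |
|---|---|---|---|
| 10% | 75% | 30.0% | 9% |
| 20% | 75% | 35.0% | 22% |
| 30% | 60% | 35.5% | 24% |
| 30% | 75% | 40.0% | 42% |
| 30% | 90% | 44.5% | 61% |

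**4. Whether selection of this size is plausible on the plan's own terms.** The plan expects STDR in the intervention arm to rise from 10% at screening to 25% at the first visit through differential compliance alone. That implies that STDR patients attend (0.25 × 0.90) / (0.75 × 0.10) = 3 times as often as other DR patients. The odds ratio for 50% versus 25% is (0.50/0.50) / (0.25/0.75) = 3. The plan thus accepts a selection effect on this endpoint as large, on the odds scale, as the difference it is powered to detect.

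**5. Whether the planned adjustment covers it.** Statistical analysis names age, diabetes duration, baseline visual acuity and unspecified other factors. It names neither prior examination nor referral source. Ophthalmologist referral is recorded only in the SOC arm, so a covariate for it has no intervention counterpart. Visual acuity at presentation is itself affected by stage.

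**The case against.** The text is not fully clear. Sampling speaks of standard criteria at both settings. The never-examined sentence mentions LVPEI in a clause from which words seem to be missing. The exclusions are introduced as those of the study, and Sample size refers to new patients at both sites. A reader could infer that common criteria were intended. This is also a condensed article, and its flow chart is not available here. That objection stands against any claim that the arms will certainly be recruited under different rules. It does not settle the matter, because no sentence states either condition for the SOC arm, and an ophthalmologist source sits badly with a first eye consultation.

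Prior examination of these referrals is an inference: strong for ophthalmologists, likely for the LVPEI network, stated for neither. That stands.

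Late arrival through ordinary referral routes is partly what the study means to contrast. This also stands, and it argues against simply removing two referral sources from the primary comparison, since that would take away part of routine care and change the comparator. It does not argue against equal eligibility.

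Sampling acknowledges selection bias, and the limitations mention the lack of randomisation. However, consecutive enrolment does not help when entry rules differ, and the limitation is framed as one of generalisability.

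**Conclusion.** The concern holds in this form: as written, the staging contrast cannot separate the pathway effect from a difference in eligibility, and the difference is expected to favour the intervention. In the illustration (30% already-examined referrals, 75% STDR among them, 25% in comparable patients of both arms), a 40% SOC rate and about a 42% chance of significance arise with no screening effect. All three inputs to that mixture are assumptions, the 25% being the plan's intervention figure applied to both arms.

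Two stronger readings are tempting and are not supported.

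- A reader might infer that the whole 25-point gap is a referral artefact. Solving f = 0.25 / (q − 0.25) shows that this would need already-examined referrals to be 71%, 56% or 45% of SOC DR patients at 60%, 70% or 80% STDR. That is arithmetically possible, but the document gives no referral mix and no STDR rate by source.
- A reader might infer that the bias always favours the intervention. The plan's own compliance assumption, 10% rising to 25%, is a selection that works against it.

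**What to change.** State and apply the same criteria in both arms: no prior fundus examination or photograph, no previously diagnosed DR, age 18 to 90. Record prior-examination and prior-DR status at LVPEI, and take it from records where possible for patients already enrolled. Base the primary staging comparison on SOC patients who meet these criteria, and count only them toward the 60.

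Use the referral source that is already captured in two ways: a sensitivity analysis limited to self and physician sources, and reporting of results by source. It should not serve as a blanket exclusion. Re-estimate the 50% SOC rate in eligible patients. If common criteria were always intended, say so, and reconcile ophthalmologist referral with the first-eye-consultation endpoint.

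Costs:

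- An amendment needs ethics clearance, and recruitment has run in both arms since March 2024, so some histories must be recovered from records.
- SOC recruitment would take somewhat longer. If, as assumed above, 30% of SOC DR patients did not qualify, 60 / 0.70 ≈ 86 would be needed to yield 60.
- The assumed difference will probably shrink. As an example only, a re-estimated SOC rate of 40% against 25% would need (1.298 + 0.842 × 0.654)² / 0.15² ≈ 152 per arm.
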